## 7.6 Trial assessments

Please see Table 1 for details of the timeline for trial visits and which procedures and assessments will be performed at each visit.

The following are recorded at the baseline visit and then every 24 weeks until the final visit at 96 weeks (i.e. day 1, week 24, week 48, week 72 and week 96):

- history and if necessary symptom-directed examination
- adherence to maraviroc as assessed by (i) self reported adherence through completion of a diary card and (ii) pill counting by pharmacy/research team member.
- weight and BMI
- waist circumference
- liver function, renal function, phosphate, CK, glucose (fasted at baseline, weeks 48 and 96), and lipid profile (fasted at baseline, weeks 48 and 96)(blood draw)
- FBC (blood draw)
- HIV viral load (blood draw)
- Urine dipstick macroanalysis and, for WOCBP, pregnancy testing

The following are recorded at the baseline visit and then every 48 weeks until the final visit at 96 weeks (i.e. day 1, week 48 and week 96):

- CD4/CD8 cell count and % (blood draw)
- HbA1c (blood draw)
- ELF score (blood draw)
- CLDQ:NAFLD questionnaire
- SF-36 questionnaire
- WPAI-SHP questionnaire
- Dietary and exercise history

The following is recorded at screen, week 48 and week 96:

- Fibroscan. For screening, the Fibroscan may be performed up to 42 days prior to baseline. For the week 48 and 96 visits this may be performed within 7 days of the study visit.

The following **optional investigation** will be performed at the baseline visit and at the 96 week visit:

- CT liver : spleen attenuation ratio. This may be performed within 7 days of the study visit with preference for the 7 days prior to baseline.

An additional week 4 safety visit will be required for those individuals in the maraviroc group, with the following procedures being performed:

- assessment of any drug toxicity through targeted history and, if required, examination
- liver function, renal function, CK, phosphate, glucose, full blood count (blood draw)
- HIV viral load (blood draw)

The following will be performed at screening only (if no hepatic imaging or liver biopsy result is available in the preceding 24 weeks):

- USS liver

The following will be performed at baseline only (if not available in the preceding 24 weeks):

- CCR5 tropism (blood draw)

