| Urine dip  and pregnancy test (for WOCBP)                                  | X                         | X                |                             | X                | X                | X                | X                | X                       |
| Concomitant medications                                                                | X                         | X                | X                           | X                | X                | X                | X                | X                       |

|                                                               |   |   |   |   |   |   |   |   |
|---------------------------------------------------------------|---|---|---|---|---|---|---|---|
| HIV associated conditions                              | X | X |   | X | X | X | X | X |
| Symptom & AE review                                | X | X | X | X | X | X | X | X |
| Diet and exercise history                              |   | x |   |   | x |   | X | X |
| CLDQ:NAFLD, SF36,
WPAI:SHP questionnaires          |   | X |   |   | X |   | X | X |
| ELF Score                                              |   | X |   |   | X |   | X | X |
| CD4/CD8 T cell count                                   | X |   |   |   | X |   | X | X |
| HIV-1 RNA level                                        | X |   | X | X | X | X | X | X |
| Proviral DNA Geno2Pheno
(tropism) Test |   | X |   |   |   |   |   |   |
| Haematology                                | X | X | X | X | X | X | X | X |
| Routine chemistry                          | X | X | X | X | X | X | X | X |
| Fasting chemistry                          |   | X |   |   | X |   | X | X |
| Additional chemistry                      | X |   |   |   | X |   | X | X |

|                                                       |   |   |   |   |   |   |   |   |
|-------------------------------------------------------|---|---|---|---|---|---|---|---|
| HIV, HBV & HCV serology       | X |   |   |   |   |   |   |   |
| Full liver screen                 | X |   |   |   |   |   |   |   |
| Ultrasound Liver                  | X |   |   |   |   |   |   |   |
| Fibroscan                         | X |   |   |   | X |   | X | X |

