| CT liver:spleen attenuation ratio |   | X |   |   |   |   | X |   |
| Drug dispensation                 |   | X | X | X | X | X |   |   |

- 1 Wk 4 visit only for individuals receiving maraviroc. Bloods are unfasted.
- 2 HR, RR, Temp, BP, Lying and standing BP (postural BP at screening only and to be repeated if history indicates)
- 3 Height only at screening; weight and waist circumference at every visit except week 4
- 4 Symptom directed physical examination only
- 5 Point of care urine dip for haematuria, proteinuria, glycosuria, leucocytes and nitrites
- 6 If no result within the preceding 24 weeks
- 7 Haemoglobin, white cell count and differential, eosinophils, platelets
- 8 Sodium, potassium, chloride, creatinine, urea, alanine aminotransferase (ALT), aspartate aminotransferase (AST), bilirubin, alkaline phosphatase (ALP), gamma glutamyltransferase (GGT), albumin, phosphate, CK, glucose (screening, weeks 4, 24 and 72); lipids (total cholesterol, HDL, LDL, triglycerides) (weeks 24 and 72 only)
- 9 Fasting glucose and fasting lipids (total cholesterol, HDL, LDL, triglycerides)
- 10 HbA1c
- 11 anti-HCV Ab, HCV RNA or HCV antigen, HBsAg; if no prior record of result: anti-HBcAb. HIV Ab/Ag only if no previous documented result
- 12 If no previous record of result: INR, ferritin, caeruloplasmin, copper, thyroid function, alpha-1 antitrypsin, anti-mitochondrial antibodies, anti-nuclear antibodies, anti-smooth muscle antibody, anti-liver/kidney/microsomal antibodies-1, coeliac serology
- 13 If no previous imaging (US, CT, MRI) or liver biopsy result confirming fatty liver in the preceding 24 weeks. This may be performed at any point between the screening and baseline visits.
- 14 Includes both median stiffness and controlled attenuation parameter scores. This may be performed at any point between the screening and baseline visits. For the week 48 and 96 week visits, to be performed within 7 days of the study visit.
- 15 Optional. To be performed within 7 days of the study visit. Preference is for the 7 days prior to baseline.
- 16 Only for individuals assigned to the maraviroc group

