## 6 ELIGIBILITY CRITERIA

### 6.1 Inclusion criteria

- (1) Aged 18 years and older
- (2) HIV-1 infected with durably suppressed ( $\geq 6$  months) HIV VL ( $<50$  copies/ml)  
  
NB. One HIV VL blip (50-200 copies/ml) is allowed in the 6 months prior to screen.
- (3) Has evidence of NAFLD on hepatic imaging (USS, CT or MRI) or liver biopsy either at screen or in the 6 months prior to screen
- (4) Provides written, informed consent to participate
- (5) Is willing to comply with the protocol requirements
- (6) If female and of child bearing potential, is using effective birth control methods (as agreed by the investigator) and willing to continue practicing these birth control measures during the trial and for at least 30 days after the end of the trial.

**Note:** Women who are postmenopausal for least 2 years, women with a total hysterectomy, and women who have a tubal ligation are considered of non-childbearing potential

- (7) **If male, and sexually-active with female partners of child bearing potential, is using effective barrier contraception**, and willing to continue using this during the trial and for at least 30 days after the end of the trial

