## 6.2 Exclusion criteria

- (1) Severe cardiovascular disease including known angina or history of myocardial infarction
- (2) History of postural hypotension, defined as a reduction in the systolic blood pressure of  $\geq 20$ mmHg after standing for at least one minute
- (3) Individuals previously exposed to MVC
- (4) HIV viral load detectable ( $\geq 50$  copies/ml). One blip (VL 50-200 copies/ml) within 6 months prior to screen is allowed.
- (5) Current HCV or HBV (HBcAb-positive, HBsAg-negative is permitted; anti-HCV Ab positive with HCV RNA or HCV antigen negative for  $\geq 6$  months following treatment or spontaneous clearance is permitted)
- (6) Other chronic liver disease including but not exclusively: cirrhosis, alcohol-related liver disease, autoimmune hepatitis, primary biliary cirrhosis, primary sclerosing cholangitis, haemochromatosis, Wilson's disease, alpha-1 antitrypsin deficiency, non-cirrhotic portal hypertension, drug-induced as deemed by a hepatologist  
Note: alcohol-related liver disease includes liver disease in the presence of excess alcohol intake as defined according to EASL guidelines 2016 (ie  $>20$ g/day or  $>17$  units/week for women and  $>30$ g/day or  $>26$  units/week for men).
- (7) ALT or AST  $> 5$ x the ULN (where ULN is defined as 41 IU/L)
- (8) Severe renal insufficiency (creatinine clearance  $< 30$  mL/min)
- (9) HIV-2 infection
- (10) Known allergy or intolerance to MVC or its constituents including hypersensitivity to peanuts or soya
- (11) If female, pregnancy or breastfeeding

(12) Individuals currently taking medications or herbal agents that are contraindicated with MVC including St John's Wort.

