#### **7.1.2 Screening Visit**

Potentially eligible participants will be invited to attend for an appointment, having been provided with a participant information sheet. Adequate time (at least 24 hours) will be allowed for questions and to consider the study before agreeing to participate. The investigator or designee will provide adequate explanation of the aims, methods, objectives and potential hazards of the study. It will also be explained to the individual that they are free to refuse or withdraw from the study for any reason without detriment to their future care or treatment. Written, informed consent will then be taken by the investigator or co-investigator and this is mandatory prior to any study procedures

. The following evaluations must be performed within 42 days prior to randomisation:

- assessment of subject eligibility according to the inclusion and exclusion criteria
- demographics

- medical history including HIV-associated conditions, nadir CD4 count, alcohol assessment, recreational drug history and history of liver disease including result of any previous liver biopsy
- full antiretroviral history
- review of non-antiretroviral medication (any medication taken within the last 28 days)
- history of allergies, both drug and non-drug
- physical examination including height, weight and waist circumference
- vital signs (pulse, respiratory rate, lying and standing blood pressure, temperature)
- urine: macroanalysis and, for women of child bearing potential, urine pregnancy test
- laboratory confirmation of HIV-1 infection (only if documentation of such confirmation does not already exist)
- hepatitis B surface antigen and hepatitis C antibody and either HCV RNA or HCV antigen
- laboratory evaluations: full blood count, urea, electrolytes, glucose, liver function, creatinine kinase (CK), phosphate, HbA1c
- full liver screen if none previously recorded (ferritin, caeruloplasmin, copper, anti-SMA, AMA, ANA, anti-LKMA, coeliac serology, alpha-1 antitrypsin, clotting, thyroid function)
- CD4/CD8 counts and %
- HIV-1 RNA by licensed assay
- ECG
- USS liver (if no hepatic imaging or liver biopsy result is available within the preceding six months)
- Fibroscan

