## 7.5 Baseline data

The following baseline visit data will be collected:

- ☐ Targeted physical examination including BMI, weight, waist circumference
- ☐ Concomitant medicines check
- ☐ Blood draw for FBC, U+Es, LFTs, phosphate, CK,
- ☐ Blood draw for ELF score
- ☐ Blood draw for HIV-1 CCR5 coreceptor tropism (if no result in the previous 24 weeks)
- ☐ Urinary pregnancy test (WOCBP only) and dipstick
- ☐ eCRF completion including data transfer
- ☐ CLDQ:NAFLD, SF36, WPAI:SHP questionnaires
- ☐ Dietary history (daily intake of olive oil, fruit, vegetables or salad, legumes, fish, wine, meat, white bread, rice and whole-grain bread)[23] and exercise history (**number of times per week exercise is undertaken, number of minutes of exercise per episode and type of exercise**)
- ☐ Fasted glucose
- ☐ Fasted lipids (total cholesterol, LDL, HDL, triglycerides)
- ☐ CT liver : spleen attenuation ratio (*optional*) following the protocol for an unenhanced CT abdomen. This may take place within 7 days of the baseline visit, with preference for the 7 days prior.

At baseline, all individuals will also be offered appropriate standard of care interventions regarding their NAFLD diagnosis in line with current NICE guidelines [4]. This will consist of advice regarding dietary modification including offer of referral to dietician; advice regarding exercise recommendations; advice regarding alcohol consumption with respect to national recommended limits and offer of referral to alcohol services where indicated. In addition, referral to the HIV/hepatology joint clinic or other specialist service will be recommended where appropriate.

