#### **8.10 Trial restrictions**

For women of child bearing potential, contraception needs to be used for the duration of the study. This includes the following, according to the woman's preference and DDIs with concomitant medications:

- Intrauterine Device (IUD)

- Hormonal based contraception (pill, contraceptive injection, implant, IUS etc.)
- Double Barrier contraception (condom and occlusive cap e.g. diaphragm or cervical cap with spermicide)
- True abstinence

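### The preferred timing of the optional research CT puts it before the baseline pregnancy test, and the protocol does not require a negative test before the scan

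*Protocol*

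**What the plan says.** Three places in the protocol set the timing of the CT, and they agree. Section 7.5, on the baseline scan: "This may take place within 7 days of the baseline visit, with preference for the 7 days prior". Section 7.6, on both scans: "This may be performed within 7 days of the study visit with preference for the 7 days prior to baseline". Table 1, footnote 15: "Optional. To be performed within 7 days of the study visit. Preference is for the 7 days prior to baseline".

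Pregnancy testing is tied to visits. Section 7.1.2 lists at screening "urine: macroanalysis and, for women of child bearing potential, urine pregnancy test", and screening may be up to 42 days before randomisation. Section 7.5 repeats the urine test at the baseline visit. Section 7.6 and Table 1 schedule it again at weeks 24, 48, 72 and 96; Table 1 also has it at early termination, where no CT is planned.

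The related safeguards are:

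- Section 6.2 excludes: "If female, pregnancy or breastfeeding".
- Section 6.1, criterion 6, requires: "If female and of child bearing potential, is using effective birth control methods (as agreed by the investigator".
- Section 8.10 adds: "For women of child bearing potential, contraception needs to be used for the duration of the study".
- Appendix 1 treats the CT as a radiation exposure, names cancer as the hazard, and gives the optional nature of the scan as the mitigation.

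**The concern.** The CT is the only research procedure in the protocol that uses ionising radiation. The baseline pregnancy test is the last scheduled check of the pregnancy exclusion before treatment starts. By asking for both a screening and a baseline test in women who must already be using contraception, the protocol does not treat contraception plus the screening test as enough before maraviroc is dispensed. The stated preference nevertheless places the abdominal scan ahead of that second check. A woman whose baseline test is positive would be found ineligible only after she had been scanned for research.

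The mitigation in Appendix 1 does not meet this case, because the freedom to decline does not protect a woman who does not know she is pregnant. Nor does any sentence bar the week-96 scan in a participant who becomes pregnant on study. Section 7.7 says that study medication may be stopped for pregnancy, and that subjects who stop it should if possible stay in follow-up and continue the required procedures. The CT is optional rather than required, but it is not expressly ruled out.

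**Working it through.** The protocol states no figure to reproduce. The check is date arithmetic on its own windows.

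**Inputs**

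- Screening: up to 42 days before randomisation, which takes place at the baseline visit (sections 7.1.2 and 7.3).
- CT: within 7 days of the visit; at baseline the 7 days before are preferred (sections 7.5 and 7.6; Table 1, footnote 15).
- Pregnancy tests: screening, baseline, then every 24 weeks (Table 1, section 7.6).
- Week-72 and week-96 visits: each ±7 days (Table 1).

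**Baseline scan, preferred order.** With screening *s* days and the CT *k* days before baseline, the age of the last scheduled test is *s* − *k*, with *k* from 1 to 7.

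- *s* = 42, *k* = 7: 42 − 7 = 35 days.
- *s* = 42, *k* = 1: 42 − 1 = 41 days.
- A smaller *s* shortens the gap, down to 0 when screening and CT fall on the same day.

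**Week-96 scan before the visit (allowed, not preferred).** The last scheduled test is at week 72.

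- Nominal interval: (96 − 72) × 7 = 168 days. Test age: 168 − 7 = 161 to 168 − 1 = 167 days (23.0 to 23.9 weeks).
- Longest: week 72 done 7 days early (504 − 7 = 497), week 96 done 7 days late, CT the day before (672 + 7 − 1 = 678). 678 − 497 = 181 days (25.9 weeks).
- Shortest, with the CT 7 days before the visit: week 72 done 7 days late (504 + 7 = 511), week 96 done 7 days early (672 − 7 − 7 = 658). 658 − 511 = 147 days (21.0 weeks).

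| CT timing | Last scheduled test | Age of test at scan |
|---|---|---|
| Baseline, days -7 to -1, screening at day -42 | Screening | 35–41 days |
| Baseline, days -7 to -1, later screening | Screening | Shorter, down to 0 |
| Week 96, 1–7 days before the visit, nominal dates | Week 72 | 161–167 days |
| Week 96, 1–7 days before the visit, all visit windows | Week 72 | 147–181 days |

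A scan done after the test at the visit itself does not have this gap; it follows that test by at most 7 days.

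**Is the scan conditional on a test anywhere?** Sections 7.5 and 7.6, footnote 15 and Appendix 1 are the places that give instructions on the CT. None asks for a negative pregnancy test first.

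**The case against.** The strongest reply is that this is silence rather than error. Section 7.5 refers to a protocol for the unenhanced abdominal CT, which is not shown, and a pre-scan pregnancy check could well be in it. The three timing statements are consistent, and the preference has a sound reason: it obtains the baseline scan before maraviroc is dispensed. Protection already exists. A negative screening test is needed to proceed, pregnancy is an exclusion, effective contraception is mandatory, and the scan can be declined. A pregnant woman would be scanned only if she had an undetected pregnancy despite contraception and an earlier negative test, accepted the optional scan, and had it before the visit's own test. The 41 days is a worst case, and the much longer week-96 gap belongs to an order that the protocol permits but does not prefer.

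Much of this stands. The probability is low, the document gives no number of women at risk, and the week-96 figures should not drive the weight of the point. Local radiology practice may close the gap. But the protocol itself recommends the order that creates the gap, for a research exposure at several sites, and nothing in its text puts a test before the scan. The reason for the preferred timing is also no obstacle, since a same-day test leaves that timing unchanged.

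**Conclusion.** The concern holds. Following the stated preference puts the baseline research CT ahead of the baseline pregnancy test, so it relies on a screening result that is 35 to 41 days old when screening is at the edge of its window and fresher otherwise. At week 96 the permitted but not preferred order gives 161 to 167 days nominally, and 147 to 181 days across the visit windows.

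These figures assume that no test is done beyond those scheduled; a check in the imaging procedure or at a local radiology department would remove the gap where it exists. The documents do not give the number of women of child-bearing potential or of scans done before a test, so no number of affected participants can be stated. The point concerns participant safety and scheduling. It does not touch the sample size or the analysis, and it is worth correcting because the correction is so cheap.

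**What to change.** In sections 7.5 and 7.6 and in Table 1, footnote 15, require for women of child-bearing potential a negative urine pregnancy test on the day of the CT, before the scan. The age of the test at the scan then becomes 0 days and the preferred pre-baseline timing stays. State also that no research CT is done in a pregnant participant, and add fetal exposure to the CT row of the risk table in Appendix 1.

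The alternative is to do the CT only on or after the visit, once that visit's test is negative, within the existing 7 days. At baseline this could put the scan up to 7 days after maraviroc is dispensed, so the same-day test is the better choice there; at week 96 either would do.

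The cost is one sentence in each of three places, one entry in Appendix 1, and at most one extra urine test per woman for each scan done before a visit.

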### **Early termination visit**

Those individuals who withdraw from the study early will be requested to attend an early termination visit, during which the following assessments will be performed:

- history and examination
- adherence to maraviroc as assessed by (i) self reported adherence and (ii) pill counting by pharmacy/research team member.
- weight and BMI
- waist circumference
- liver function, renal function, CK, phosphate, fasting glucose, HbA1c and fasting lipid profile (blood draw)
- FBC (blood draw)
- HIV viral load (blood draw)
- ELF score (blood draw)
- Urine dipstick for macroanalysis and, for WOCBP, pregnancy testing
- CLDQ:NAFLD questionnaire
- SF-36 questionnaire

- WPAI-SHP questionnaire
- Dietary and exercise history
- Fibroscan

### 7.7 Withdrawal criteria

A subject is free to withdraw from the study at any time. In addition, the Investigator may decide, for reasons of medical prudence, to withdraw a subject. If a subject discontinues study medication dosing, every attempt should be made to keep the subject in the study and continue to perform the required study-related procedures and follow-up procedures. If this is not possible or acceptable to the subject or Investigator, the subject may be withdrawn from the study.

Study medication may also be discontinued in the following instances:

1. If the subject withdraws his/her consent.
2. If the investigator considers in the interest of the subject (i.e. intercurrent illness, unacceptable toxicity) that it is best for them to withdraw their consent.
3. The subject fails to comply with the protocol requirements or fails to cooperate with the investigator.
4. Pregnancy during the course of the study.

The date and reasons for the withdrawal will be clearly stated on the subject's eCRF and source document. Every attempt should be made to arrange follow up visits for subjects who are withdrawn from the trial (including where individuals fall pregnant).

Subjects withdrawing from the trial may be replaced if considered necessary by the Chief Investigator.

